**LIST OF ABBREVIATIONS AND RELEVANT DEFINITIONS**

| **ABR** | **ABR form, General Assessment and Registration form, is the application form that is required for submission to the accredited Ethics Committee (In Dutch, ABR = Algemene Beoordeling en Registratie)** |
| --- | --- |
| **AE** | **Adverse Event** |
| **AR** | **Adverse Reaction** |
| **CA** | **Competent Authority** |
| **CCMO** | **Central Committee on Research Involving Human Subjects; in Dutch: Centrale Commissie Mensgebonden Onderzoek** |
| **CV** | **Curriculum Vitae** |
| **DSMB** | **Data Safety Monitoring Board** |
| **EU** | **European Union** |
| **EudraCT** | **European drug regulatory affairs Clinical Trials** |
| **GCP** | **Good Clinical Practice** |
| **IB** | **Investigator’s Brochure** |
| **IC** | **Informed Consent** |
| **IMP** | **Investigational Medicinal Product** |
| **IMPD** | **Investigational Medicinal Product Dossier** |
| **METC** | **Medical research ethics committee (MREC); in Dutch: medisch ethische toetsing commissie (METC)** |
| **(S)AE** | **(Serious) Adverse Event** |
| **SPC** | **Summary of Product Characteristics (in Dutch: officiële productinfomatie IB1-tekst)** |
| **Sponsor** | **The sponsor is the party that commissions the organisation or performance of the research, for example a pharmaceutical**  **company, academic hospital, scientific organisation or investigator. A party that provides funding for a study but does not commission it is not regarded as the sponsor, but referred to as a subsidising party.** |
| **SUSAR** | **Suspected Unexpected Serious Adverse Reaction** |
| **Wbp** | **Personal Data Protection Act (in Dutch: Wet Bescherming Persoonsgevens)** |
| **WMO** | **Medical Research Involving Human Subjects Act (in Dutch: Wet Medisch-wetenschappelijk Onderzoek met Mensen** |

**SUMMARY**

**Rationale:** Evidence is accumulating that mind-body therapies can be used as effective and safe adjuncts to medical treatment for a number of common clinical conditions. Some studies suggest that mindfulness training (also known as mindfulness-based stress reduction or mindfulness meditation) may have a beneficial clinical effect in patients with cardiovascular disease or those at increased cardiovascular risk. In addition, psychological problems and symptoms of depression and anxiety appear to be amenable to mindfulness meditation. Adult patients with structural heart disease have a high incidence of both physical (cardiac) and psychological problems and may therefore benefit from mindfulness training.

**Objective**: Objective of this study is to determine whether mindfulness training has beneficial clinical and psychological effects when provided as adjunct to usual care, and whether offering the training is effective and cost-effective, in adult patients with structural heart disease (congenital heart disease or cardiomyopathy).

**Study design:** Pragmatic randomized controlled single-blind trial.

**Study population:** Adults 18 years and older known to have structural heart disease. Exclusion criteria: patients in whom an operation or percutaneous intervention is planned, patients unable or unwilling to give informed consent, those without internet access, those unable to read or write Dutch. To demonstrate an improvement of 5% in the active intervention group vs 1% in the control group in exercise tolerance requires 330 patients.

**Intervention**: Mindfulness-training complementary to usual care. The mindfulness training consists of online sessions with assignments and practice supplemented with intermittent supportive email and text messages. The control group will receive usual care which includes lifestyle advice.

**Main study parameters/endpoints:** Primary outcome will be differences between the active intervention and control groups in the mean improvement, compared to baseline, of age- and sex expected exercise tolerance (6 minute walk test). The intention-to-treat analysis will address the question whether offering the training is effective. The as-treated analysis will evaluate the treatment effect depending on the degree of adherence. Secondary outcomes will be heart rate, blood pressure, and resting respiratory rate (markers of cardiac fitness), NTproBNP (a biomarker for heart failure), cumulative cortisol in 2 cm of hair taken from the scalp (cumulative measure of stress), a composite endpoint (all-cause mortality, heart failure, arrythmia, myocardial infarction, cardiac surgery, percutaneous cardiac intervention, electrical cardioversion), quality-of-life, psychological well-being, preference values, health care costs, and non-health care costs.

**Nature and extent of the burden and risks associated with participation, benefit and group relatedness:**

All patients will be given usual care which includes lifestyle advice. Patients in the active intervention group will be offered an online training for the duration of 12 weeks with email messages and assignments 1-3 times per week, followed by reminder messages once every 2-4 weeks for another 40 weeks. At baseline, 3-months, and 1 year all patients will undergo a 6 minute walk test and blood tests, one scalp hair will be taken, and they will be asked to fill out quality-of-life, psychological well-being, medical resource use and cost questionnaires.

# INTRODUCTION AND RATIONALE

Evidence is accumulating that mindfulness training and related mind-body therapies can be used as effective and safe adjuncts to medical treatment for a number of common clinical conditions including depression, insomnia, anxiety, post-traumatic stress, irritable bowel syndrome, nausea, pain, diabetes, hypertension, and cardiovascular disease [1-5]. Several publications report physiological effects of mind-body practices by modifying the response to chronic stress, including beneficial changes in respiration rate, heart rate, oxygen consumption, blood pressure, inflammatory markers, and brain activity. The biological pathway is through the autonomic nervous system. Neuroendocrine, endothelial, and immune system function all appear to be beneficially effected [3, 6-7]. Functional MRI performed during meditation or prayer demonstrates specific areas of increased or decreased activity [8-10]. Long-term structural changes in the brain have also been demonstrated among meditators and religious practitioners [11-12]. There are even data suggesting that gene expression is effected [13].

Some studies suggest that mindfulness training (also known as mindfulness-based stress reduction or mindfulness meditation) may have a beneficial clinical effect in patients with cardiovascular disease or those at increased cardiovascular risk [4, 14-15]. In addition, psychological problems and symptoms of depression and anxiety appear to be amenable to mindfulness meditation [3, 16-17]. Adult patients with structural heart disease have a high incidence of both physical (cardiac) and psychological problems and may therefore benefit from mindfulness training [18-19].

# OBJECTIVES

Primary Objective of this study is to determine whether mindfulness training has beneficial clinical and psychological effects in adult patients with structural heart disease (congenital heart disease or cardiomyopathy).

Secondary Objective is to determine whether offering mindfulness training is effective and cost-effective in adult patients with structural heart disease.

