### Flowchart

Justification of no placebo online training in the control group and single-blinded design:

(A1) We consider the placebo effect of the online training as being part of the active intervention as it would be implemented in real-world practice which implies that the study will measure effectiveness rather than efficacy and that it is pragmatic rather than explanatory.

(A2) The inclusion of the placebo effect as part of the active intervention compared to usual care without placebo in the control group is further justifiable as no competing therapy exists.

(A3) Any placebo online training that we develop is likely to have some beneficial effect, due to non-specific therapeutic mechanisms like structure, hope and working alliance. Such beneficial effect in the control group will reduce the measured difference in effectiveness and would not be an accurate reflection of what can be expected in real-world practice.

(A4) Blinding of patients to the intervention itself is impossible since they are themselves actively participating in the online training.

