## Intention-to-treat and as-treated analysis

An intention-to-treat analysis will be performed to address whether offering mindfulness training is effective and cost-effective. Patients that are non-adherent to the offered training (cross-overs to usual care) will be analyzed as part of the active intervention group. Similarly, control patients who seek interventions on their own will be analyzed in the usual care group to which they were allocated.

An as-treated analysis will be performed to address whether mindfulness training is beneficial if actually performed and the treatment effect depending on the degree of adherence. The usual care group will consist of the control group. In the active intervention group, adherence to the intervention is monitored (see ‘’Intervention’’) and completion of sufficient number of training modules will be the criterion to determine which patients in the active intervention arm are included in the ‘’on-treatment’’ group. The ‘’on-treatment’’ group will consist of those patients who complete 50% or more of the exercises in the first 12 weeks. Patients who start the mindfulness training but complete less than 50% of the assignments in the first 12 weeks will be considered non-adherent and analyzed separately as the “partially treated’’ group. We will also evaluate outcome as function of the proportion of completed exercises as a continuous variable adjusting for potential confouders in a multivariable model. Finally, we will use the method developed by Robins and Tsiatis that corrects for non-compliance in randomized trials using rank preserving structural failure time models [25-26].

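### Section 2 conflicts with the rest of the protocol: its primary objective matches the as-treated question, its secondary objective matches the intention-to-treat question, and no primary analysis is named

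*Protocol*

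**What the plan says.** The protocol distinguishes the training from the offer of the training, and ranks the two.

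- **Section 2, primary objective:** "Primary Objective of this study is to determine whether mindfulness training has beneficial clinical and psychological effects".
- **Section 2, secondary objective:** "Secondary Objective is to determine whether offering mindfulness training is effective and cost-effective in adult patients with structural heart disease".
- **Section 9.2, ITT:** "An intention-to-treat analysis will be performed to address whether offering mindfulness training is effective and cost-effective".
- **Section 9.2, as-treated:** "An as-treated analysis will be performed to address whether mindfulness training is beneficial if actually performed". The on-treatment "group will consist of those patients who complete 50% or more of the exercises in the first 12 weeks", and the comparator is the control group.
- **Summary, main endpoints:** "The intention-to-treat analysis will address the question whether offering the training is effective".

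Other sections describe a randomised, pragmatic comparison. Section 7.1.1 defines the primary outcome as the difference between the active and control groups in mean improvement on the walk test. Section 7.2 defines the active arm as the offer of training plus usual care, allocated 2:1. The justification in section 7.2.1 says that "the study will measure effectiveness rather than efficacy and that it is pragmatic rather than explanatory", and section 7.4 counts non-adherence as part of that effectiveness. The sample size calculation in section 4 gives 99 control and 198 active patients for power 0.90. It then adds a power of 0.80 for the as-treated comparison if half of the active arm adheres.

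**The concern.** The objective ranked first is worded like the question given to the analysis that randomisation does not protect. The objective ranked second is worded like the question given to the analysis that it does protect. The ITT sentence in section 9.2 repeats the secondary objective almost word for word, so the pairing does not look like a stray choice of terms.

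The on-treatment group is selected by what patients do in the 12 weeks after randomisation, yet it is compared with all controls. Patients who complete the exercises may be more motivated or in better health than the average control, and may improve more whatever the training does. Section 9.2 mentions confounder adjustment only for the model with adherence as a continuous variable, not for this group comparison.

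The two analyses could well disagree, because the protocol itself plans for adherence as low as 50%. If as-treated were positive and ITT null, a report could cite section 2 and claim that the primary objective was met.

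**Working it through.** **1. Objectives against analyses**

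| Section 2 | Its subject | Section 9.2 analysis with the matching question | Groups as randomised? |
|---|---|---|---|
| Primary | the training | as-treated | no |
| Secondary | offering the training | ITT | yes |

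**2. The rest of the protocol**

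| Place | Comparison it supports |
|---|---|
| 7.1.1, primary outcome | active versus control group |
| 7.2, arm definition | offer plus usual care versus usual care |
| 7.2.1 and 7.4, rationale | effectiveness, non-adherence included |
| Section 4, main calculation | full 2:1 arms |

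The second table points to ITT throughout, whereas the first points the primary objective to as-treated. No sentence settles which analysis is primary.

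**3. Reproducing the sample size**

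Inputs from section 4: difference 5 − 1 = 4 points, SD 10, alpha 0.05, power 0.90, ratio 2:1. Sidedness is not stated. Two-sided reproduces the figures; one-sided would give 81 controls.

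- Controls: (1 + 1/2) × (1.960 + 1.282)² × 10² / 4² = 98.5, so 99, with 198 active. This agrees with the protocol.
- Power at 99/198: SE = 10 × √(1/99 + 1/198) = 1.231; 4/1.231 = 3.250; Φ(3.250 − 1.960) = 0.901.
- As-treated, 99 versus 99: SE = 10 × √(2/99) = 1.421; 4/1.421 = 2.814; Φ(2.814 − 1.960) = 0.804, against the stated 0.80.

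The main calculation is therefore for the randomised arms. The as-treated figure is a fallback that carries the same 4-point difference over to adherers.

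**4. Illustration of the risk**

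Suppose the training has no effect, but adherers would improve b points more than controls anyway. The protocol gives no value for b, so 1, 2 and 3 are assumptions. The two-sided rejection rate of the 99 versus 99 test is 1 − Φ(1.960 − b/1.421) + Φ(−1.960 − b/1.421).

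| b (assumed) | b/1.421 | Rejection rate |
|---|---|---|
| 0 | 0 | 5% |
| 1 | 0.704 | 10.8% |
| 2 | 1.407 | 29.1% |
| 3 | 2.111 | 56.0% |

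**5. Power once ITT is named primary**

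If the 4 points are the mean difference across everyone offered training, power is 0.90 at 99/198. It is 0.93 if all 330 are analysed as 110/220 (SE 1.168; Φ(3.425 − 1.960)). If the 4 points applied only to adherers and non-adherers improved like controls, 50% adherence would halve the ITT difference to 2 points. Power would then be 0.37 at 99/198 and 0.40 at 110/220. The protocol does not state that second assumption.

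**The case against.** A reader might infer that ITT serves only the secondary objective, and that the trial's main conclusion will therefore not rest on randomisation. The protocol does not support going that far. Neither statement is written anywhere. The qualifier about the training being performed appears in section 9.2, not in section 2, and asking whether a training has beneficial effects is also ordinary wording for a question that a randomised comparison answers. The primary outcome, the arm definition, the rationale and the main power calculation all favour ITT. ITT is named before as-treated both in the Summary and in section 9.2, and the Summary states one unranked objective covering both questions. A positive as-treated result would satisfy the primary objective only if the defined primary outcome were set aside. This part of the objection stands, and it makes the finding a contradiction that permits a biased reading, not a plan that requires one.

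It can also be said that section 9.2 does not leave the question of benefit when performed to a naive comparison, since it plans a rank-preserving structural model that respects randomisation. That is correct, but the model is for failure times and does not settle the analysis of a continuous walk-test outcome.

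Two further limits apply. The values of b are assumed, so the rejection rates show scale only. Testing at both 3 months and 1 year raises a multiplicity question, but it is a separate issue that reordering the objectives would not resolve, and it is no measure of this defect.

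The mention of psychological effects in the primary objective is a lesser matter. Section 7.1.1 explains why a physical endpoint was chosen, and SF-36 and the anxiety and depression scale are secondary outcomes. The objective is simply broader than its endpoint.

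Leaving detail to a statistical analysis plan does not answer the point, because the protocol itself fixes both the ranking of the objectives and the question each analysis addresses.

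**Conclusion.** The point holds as an internal contradiction. Section 2 ranks the objectives in a way that, read with section 9.2, ties the primary one to a non-randomised comparison. The primary outcome, arm definition, pragmatic rationale and sample size rest on the randomised arms, and no primary analysis is named. The conclusion that the main claim will leave randomisation is not established.

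The textual finding needs no assumption. Its possible size does: with SD 10, groups of 99, no true effect and adherers improving 1 or 2 points more regardless, the as-treated test is significant in 11% or 29% of trials instead of 5%. The protocol's own sample size figures reproduce and are not in question here.

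**What to change.** - **Section 2, primary objective:** whether offering online mindfulness training plus usual care, compared with usual care alone, improves 6-minute walk performance expressed as a percentage of that expected for age and sex.
- **Section 2, secondary objectives:** the effect of the training when performed, the psychological effects, and cost-effectiveness.
- **Section 9.2:** state that ITT on the randomised arms is the primary analysis and that the as-treated analysis is supportive.
- **Summary:** bring the objective into line.

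The cost is an amendment to the text. No data, visits or patients are added, and no change in sample size is needed so long as the 4-point difference is meant for everyone offered training, which a short statement in section 4 could confirm. The change should be made before anyone sees results by arm.

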# STUDY DESIGN

Pragmatic randomized controlled single-blind trial.

Duration: 12 months

Setting: outpatient clinic of an academic hospital

# STUDY POPULATION

**Population (base)**
The source population are adult patients attending the ErasmusMC cardiology outpatient clinic for follow-up and monitoring of their structural heart disease, including those with congenital heart disease and those with cardiomyopathy.

**Inclusion criteria**

1. Adults 18 to 65 years old known to have structural heart disease, including congenital heart disease and cardiomyopathy.

**Exclusion criteria**

1. planned operation or percutaneous intervention
2. inability or unwillingness to give informed consent
3. inability to understand Dutch, inability to read or write Dutch
4. no internet access or no email or no cell phone.
5. patients who do not fill out their baseline questionnaires or do not show up for the scheduled baseline tests

**Sample size calculation**

To demonstrate an improvement of 5% in the active intervention group vs 1% in the control group in exercise tolerance (expressed in percentage exercise tolerance compared to what can be expected given the patient’s age and sex) would require 99 patients in the control group and 198 in the active intervention group (SD10%, alpha=0.05, power=0.90, ratio experimental to controls=2). Even if only 50% of patients in the experimental group adhere to the training, we would in the as-treated analysis compare three groups of each 99 patients, which would give us a power of 0.80. To account for non-adherence and loss to follow-up a total of 330 patients will be randomized. This number of patients will be sufficient to demonstrate a smaller difference (5% vs 2%) in a repeated measurements analysis with a power of 75-90% (2 follow-up measurements, correlation between follow up measurements=0.70, correlation between baseline & follow-up=0.50).

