## Randomisation, blinding and treatment allocation

(see flowchart on next page)

All potentially eligible patients are asked to participate in a randomized controlled trial. Written informed consent is obtained for extra data collection alongside usual care and for randomization to one of two healthy lifestyle programs. Patients are explained that mindfulness training is the active intervention and that they will have a 50% chance to be randomized to the active intervention group. The general principle of mindfulness is explained and patients are informed that the training is a web-based online training with exercises that they need to do themselves. Further details about the training and how to access the website and their login will be given after randomization.

Patients will be randomized to either offering online mindfulness training plus usual care (active intervention) vs usual care only (control) (which includes advice about a healthy lifestyle). Patients will be randomly assigned to the active intervention (offering mindfulness training plus usual care) vs control (usual care) in the ratio 2:1 to compensate for non-adherence with the intervention. Randomization will be performed by computer using dedicated software designed for this purpose. Block randomization will be used. The block size will be undisclosed until trial completion.

Patients will not be blinded to the intervention itself since they are actively participating in it. They will, however, be asked to avoid describing their training during follow-up visits to other patients, physicians, and investigators in order to ensure single-blinding. To blind investigators, the treatment allocation will remain undisclosed to the observer assessing outcomes and during data analysis. We will confirm observer blinding by asking the assessor of the exercise tolerance tests which treatment arm he/she thinks the patient has been allocated to.

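### The 330 patients are said to allow for non-adherence, but the margin over the required 297 equals a 10% loss allowance, and ITT power at the plan's own 50% adherence case is not given

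*Protocol*

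**What the plan says.** All references are to the protocol.

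- **Section 4, sample size calculation.** The target is set as "To demonstrate an improvement of 5% in the active intervention group vs 1% in the control group in exercise tolerance", with "SD10%, alpha=0.05, power=0.90, ratio experimental to controls=2". This "would require 99 patients in the control group and 198 in the active intervention group".
- **Same section, adherence case.** "Even if only 50% of patients in the experimental group adhere to the training, we would in the as-treated analysis compare three groups of each"; the group size is given as 99 and the power as 0.80.
- **Same section, inflation.** "To account for non-adherence and loss to follow-up a total of 330 patients will be randomized". Neither a loss rate nor a non-adherence rate is given.
- **Same section, smaller effect.** The number is said to be "sufficient to demonstrate a smaller difference (5% vs 2%) in a repeated measurements analysis with a power of 75-90" per cent, with two follow-up measurements, correlation 0.70 between follow-ups and 0.50 between baseline and follow-up.
- **Section 7.2.** Allocation is "in the ratio 2:1 to compensate for non-adherence with the intervention".
- **Section 9.2.** For the ITT analysis: "Patients that are non-adherent to the offered training (cross-overs to usual care) will be analyzed as part of the active intervention group". The same section assigns to ITT the question whether offering the training works.

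**The concern.** ITT keeps non-adherers in the active arm, so any shortfall in their benefit shrinks the difference being tested. An allowance for non-adherence therefore has to appear either as a smaller assumed ITT difference or as a larger sample. The only sample-size addition is 33 patients (330 − 297), and the section does not say how it is divided between loss and non-adherence. For its one adherence scenario the section gives as-treated power only. That comparison sets a self-selected group of adherers against all controls, so it does not stand in for the randomised comparison.

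The risk lies in how a null ITT result would be read. If non-adherence is heavy, it could be taken to show that offering the training does not work when it reflects low power. Section 9.6 also makes the long-term economic model conditional on the trial indicating effectiveness, so a false negative would stop that work too.

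**Working it through.** **Inputs (section 4):** difference 5 − 1 = 4 points; SD 10; alpha 0.05; power 0.90; ratio 2:1; 330 randomised; adherence case 50%. Sidedness is not stated: two-sided reproduces the plan's 99 controls, one-sided gives 81, so two-sided is used. Power is Φ(difference/SE − 1.96).

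**1. The plan's own figures**

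- Controls: (1 + 1/2) × (1.96 + 1.2816)² × 10² / 4² = 98.5, so 99, with 198 active and 297 in all.
- ITT, 99 vs 198: SE = 10 × √(1/99 + 1/198) = 1.231; 4/1.231 − 1.96 = 1.29; power 0.90.
- As-treated, 99 vs 99: SE = 10 × √(2/99) = 1.421; 4/1.421 − 1.96 = 0.85; power 0.80.

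Both reproduce, and both use 4 points.

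**2. What the margin covers**

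330 × 0.90 = 297. A 10% loss returns exactly the required number. The 10% is inferred from this arithmetic.

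**3. ITT difference at 50% adherence, with 4 points in adherers**

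- No benefit in non-adherers: 0.5 × 4 + 0.5 × 0 = 2 points.
- Half benefit: 0.5 × 4 + 0.5 × 2 = 3 points.
- Full benefit: 4 points, the only case that matches the plan's use of 4 points for both comparisons.

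**4. Single comparison**

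SE is 1.231 at 99/198 and 10 × √(1/110 + 1/220) = 1.168 at 110/220.

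| ITT difference | 297 patients | 330 patients |
|---|---|---|
| 2 | 0.37 | 0.40 |
| 3 | 0.68 | 0.73 |
| 4 | 0.90 | 0.93 |

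**5. Repeated measures at the plan's correlations**

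With a baseline correlation of 0.50, the variance of a change score is 100 × (2 − 2 × 0.5) = 100, so SD 10 fits both a single visit and a change. The variance factors for the mean of two follow-ups are:

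- mean change: (1 + 0.7)/2 + 1 − 2 × 0.5 = 0.85;
- baseline-adjusted (ANCOVA): (1 + 0.7)/2 − 0.5² = 0.60.

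The SD becomes 10 × √factor.

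| ITT difference | Mean change, 297 / 330 | ANCOVA, 297 / 330 |
|---|---|---|
| 2 | 0.42 / 0.46 | 0.55 / 0.60 |
| 3 | 0.75 / 0.80 | 0.88 / 0.91 |

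The 3-point row reproduces the plan's 75–90% for 5% vs 2%.

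**The case against.** The strongest reply is that the 5% may already be net of non-adherence. Section 7.4 says non-adherence belongs to what would be seen in practice and that effectiveness is the target, and section 7.2.1 calls the trial pragmatic. On that reading ITT power at 4 points is 0.90 and the as-treated 0.80 is a floor. This is possible, but the section does not say so. With 50% adherence and no benefit in non-adherers, a net 4 points would require 4/0.5 = 8 points in adherers, whereas the plan's 0.80 is computed at 4.

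Second, the 5% vs 2% sentence gives real cover. Three points is what remains at 75% adherence with no benefit in non-adherers, or at 50% adherence with half benefit. This stands and limits the concern. The plan does not, however, present that sentence as its non-adherence allowance, and it does not reach the 2-point case.

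Third, zero benefit is an assumption. Describing non-adherers as cross-overs supports it, but section 9.2 also defines a partially treated group, who may gain something. The range has to be shown.

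Four stronger readings are tempting and are not supported:

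- *That the plan claims ITT power of 0.90 at 50% adherence.* It does not. It attaches 0.90 to the 4-point difference and 0.80, as-treated, to the 50% case, which is a stress case and not an expected rate.
- *That 0.90 at 330 requires about 95% adherence.* This holds only for a single comparison with no loss. The planned mixed model with baseline adjustment gives 0.88–0.91 at 75% adherence.
- *That the plan assumes 10% loss.* It states no rate; at 5% loss about 313 would remain (330 × 0.95).
- *That 2:1 achieves nothing and should become 1:1.* At 297 patients and exactly 50% adherence, as-treated power is 0.80 either way, and 1:1 gives ITT power of 0.93 against 0.90 at 4 points. Below 50% adherence, 2:1 gives more as-treated power (0.57 vs 0.51 at 20%), and it enlarges the adherence subgroups. The choice is a trade-off.

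**Conclusion.** The point holds as an unsupported claim about what 330 covers. The section states no rate for loss or non-adherence, the margin is what a 10% loss alone would consume, and the ITT power that matters under the plan's own adherence case is absent.

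The size depends on the benefit in non-adherers and on the analysis. If non-adherers gain nothing, ITT power at 50% adherence does not exceed 0.60 under any of the analyses checked, and is as low as 0.37. If they gain half, the planned repeated-measures analysis still gives 0.75 or more. These figures rest on SD 10, two-sided 0.05, a 4-point effect in adherers, the plan's correlations for the repeated-measures values, and between 297 and 330 patients analysed. The sample size arithmetic itself is correct. What needs correcting is the property claimed for the total.

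**What to change.** In the sample size calculation of section 4:

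1. State the loss rate that 330 allows for (10% if the figure came from 297/0.90) and remove the claim that the same number also accounts for non-adherence.
2. State that ITT power of 0.90 requires a mean difference of 4 points across all randomised active patients, non-adherers included.
3. Beside the as-treated 0.80, report ITT power at 50% adherence with its assumptions: 0.37–0.40 (single comparison) and 0.42–0.60 (repeated measures) with no benefit in non-adherers; 0.68–0.73 and 0.75–0.91 with half benefit. Link the last range to the existing 5% vs 2% statement.

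Keep the 2:1 allocation. No extra patients are needed. The cost is a few sentences and a less favourable stated power.
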